## Abstract

**Background:**

Young patients aged 16 to 25 years with type 1 diabetes (T1D) often encounter challenges related to deteriorating disease control and accelerated complications. Mobile apps have shown promise in enhancing self-care among youth with diabetes. However, inconsistent findings suggest that further evidence is necessary to confirm the effectiveness of app-based interventions.

**Objective:**

This study aims to evaluate the effectiveness of the Healthcare CEO app in patients with T1D transitioning from adolescence to early adulthood.

**Methods:**

A 2 arms, double-blind, randomized controlled trial will be conducted over a 9-month period, with strategies designed to enhance treatment fidelity. The study expects to enroll 96 patients with T1D, aged 16 to 25 years. Participants will be randomly assigned to either the experimental or control group through central randomization. The intervention will be implemented using the Healthcare CEO app, which consists of 11 interfaces. The research will compare differences in disease control outcomes, confidence in self-management, self-care behaviors, emotional distress, quality of life, and specific diabetes-related knowledge between the 2 groups at baseline and 3, 6, and 9 months after intervention. Additionally, changes within the experimental group will be analyzed before and after the intervention.

**Results:**

The study was funded in August 2020. It was originally scheduled from August 2020 to July 2022 but was interrupted by the COVID-19 pandemic after enrolling 38 participants, with preliminary results anticipated for publication by November 2024. Recruitment resumed in August 2023, with findings expected to be finalized by July 2025.

**Conclusions:**

The Healthcare CEO app is a comprehensive solution tailored specifically for individuals with T1D transitioning from adolescence to early adulthood. This innovative app has the potential to improve the quality of care for adolescents with T1D during this critical stage and may serve as valuable evidence in support of app-based intervention strategies.

**Trial Registration:**

ClinicalTrials.gov NCT05022875; https://www.clinicaltrials.gov/study/NCT05022875

**International Registered Report Identifier (IRRID):**

DERR1-10.2196/59871

## Introduction

### Overview

Type 1 diabetes (T1D) is the most common type of diabetes among youth younger than 18 years [1]. The incidence of T1D has exhibited a decline in the 0-9 years age group and an increasing trend in the 10-14 years age group [2,3]. Notably, T1D accounts for approximately 0.59% of all diabetes cases in Taiwan, and its incidence in patients aged 19 years or younger is 5.17 out of 100,000 while its prevalence is 0.05%. The prevalence and incidence of T1D in patients aged 19 years or younger increased significantly from 2005 to 2014 [4]. With this increase, the demand for care during the transition phase between adolescence and early adulthood is also expected to increase [5]. Therefore, understanding the life experiences and health care needs of adolescents with T1D in this transition phase and comprehending the customization of interventions to meet these needs is crucial in T1D care.

### Background

#### Encounters and Challenges of Patients With T1D in the Transition Phase From Adolescence to Early Adulthood

A transition phase is when an individual encounters significant life events or environmental changes. It is fraught with uncertainty and requires adaptation by learning new skills and strategies [6]. In nursing, the antecedents of the transition process are transition events that can be classified into 4 categories: developmental, situational, health‐illness, and organizational transitions [6]. Moreover, providing nursing support to patients in transition may contribute to role mastery and maintenance of physical and emotional well-being [7].

The encounters and challenges of patients with T1D transitioning from adolescence to early adulthood are wide-ranging and possess unique characteristics. The developmental transition from adolescence to early adulthood is often characterized by a rapid increase in height and body weight, as well as dramatic hormonal changes. Therefore, individuals with T1D in this transition commonly face the physiological challenge of maintaining stable blood glucose levels [5,8] and are at a high risk of poor disease control [9,10]. A study of individuals registered in the T1D Exchange Clinic Registry (a large-scale registry of patients with T1D in the United States) revealed that the mean hemoglobin A_1c_ (HbA_1c_) level in 18- to 25-year-olds was 8.7% (SD 1.9%) [11], which is higher than the average. The inability to achieve optimum blood glucose control is one of the greatest stressors faced by patients with T1D and may even cause anticipatory nervousness, which in turn affects sleep quality [12]. Other key stressors include the quest for independence, the burden of disease-related self-care, and the implementation of disease self-management [13,14]. Challenges faced by young patients with T1D in situational transition include the deconstruction of peer relationships caused by education system transition, establishment of sexual relationships, worries regarding the health and genetic inheritance of offspring, and reconstruction of physician-patient relationships due to workplace changes or home relocation [13,15,16]. During health-illness transition, especially from late adolescence to early adulthood, patients often become hospitalized owing to acute complications such as ketoacidosis and hypoglycemia. The need for frequent blood glucose monitoring and the transition from hospitalization to discharge often causes disruptions to life routines [5,16,17]. Young patients with T1D often experience an organizational transition, from family-centered care to patient-centered care, at 16-25 years [18,19]. Difficulties faced during this transition period often include the lack of a comprehensive transition-phase care plan that meets patient requirements, negative health care–seeking experiences in adult care systems, termination of health insurance, and loss to follow-up [10,20,21]. In Taiwan, the pediatric care model is adopted for most patients with T1D transitioning from adolescence to early adulthood. Many patients consider the transition from pediatric to adult care unnecessary owing to trust in physician-patient relationships and the familiarity of medical environments. Moreover, approximately 25% of patients reported that physicians should engage in active discussions with patients and provide assistance for referrals to adult care [5].

#### Needs and Effectiveness of App-Based Interventions Among Patients With T1D in the Transition Phase From Adolescence to Early Adulthood

Support from health care providers and primary caregivers is crucial for patients with T1D in the transition phase [14,22]. Patients with T1D, their primary caregivers, and health care providers agree that the provision of technology-based care and the development of specific apps for T1D self-management are important health care needs that should be addressed [23,24]. Studies have shown that diabetes-related knowledge, diabetes-specific and general life stress, and emotional disorders can affect self-care behaviors, disease management effectiveness, and HbA_1c_ control among patients in the transition phase [25-28], with higher severity of emotional distress associated with poorer HbA_1c_ control and quality of life (QoL) [29,30]. Therefore, app-based intervention measures should aim to address these factors.

Among the studies on the use of app-based interventions for youth with T1D or those in the transition phase, Goyal et al [31] and Veazie et al [32] reported that app-based interventions improved HbA_1c_ levels. Additionally, Frøisland et al [33] found that app-based interventions resulted in a better understanding of disease-related knowledge, whereas app usage seemed to positively affect diabetes self-care. However, some longitudinal studies have revealed that app interventions had no significant effects on HbA_1c_ levels [34,35], frequency of hypoglycemic events [31], diabetes-related QoL [31,34], self-perceived diabetes management ability, and diabetes-related emotional distress [35]. Although young patients with T1D generally provide positive ratings for the usability and feasibility of user-centered apps [35,36], these inconsistent results indicate that further evidence is necessary to support the effectiveness of app-based interventions.

#### Knowledge Gaps

Currently, the available apps for diabetes management can be broadly classified into 5 categories: nutrition, physical activity, blood glucose monitoring, insulin titration, and insulin injection. Most apps merely possess a single function, although there is an increasing trend toward integration [37]. Additionally, the majority of Chinese-language apps provide general diabetes knowledge, which may not be applicable to adolescents or young adults, and do not cater to the specific needs of patients with T1D in the transition phase [5]. Furthermore, the effectiveness of such apps should be validated by long-term empirical evidence [24,38], and few studies have mentioned the adoption of strategies to enhance treatment fidelity [31,35]. Health apps developed for intervention should incorporate evidence-based content while fulfilling the needs and protecting the privacy of the target age groups to enhance effective disease self-management [39]. To address the specific needs of patients in the transition phase, we developed the Healthcare CEO app using a user-centered approach. This app targets challenges such as poor glycemic control; pressures related to self-care; effective disease self-management; and interpersonal issues, including the establishment of romantic relationships, concerns about the health and heredity of future generations, workplace adaptation, parent-child conflicts, and enhancing QoL. This study aims to present a comprehensive protocol for evaluating the efficacy of the Healthcare CEO app. This will involve a series of detailed analyses, including (1) comparing disease control outcomes, confidence in self-management, self-care behaviors, emotional distress, and QoL between the experimental and control groups, and (2) a comparison of differences in preintervention and postintervention disease control outcomes, confidence in self-management, self-care behaviors, emotional distress, and QoL in the experimental group.

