### Participants

#### Inclusion and Exclusion Criteria

Participants will be enrolled from the outpatient clinic and wards of the Department of Pediatric Endocrinology and Metabolism, at a medical center in Northern Taiwan. The inclusion criteria are as follows: (1) a confirmed diagnosis of T1D from an endocrinologist before the age of 16 years and a disease duration of >6 months; (2) aged 16-25 years; (3) mean HbA_1c_ level ≥7.5% one year before inclusion; (4) ability to communicate in Chinese or Mandarin; (5) owning a smartphone with internet access; (6) agreeing to voice recording while explaining the treatment process; and (7) signing the informed consent sheet prior to participation—for minors, a legal representative must provide consent and sign the informed consent sheet. Patients with T1D with concomitant metabolic diseases, chromosomal aberrations, major illnesses, and cognitive impairment will be excluded from the study because their health care needs during the transition phase may differ from those who experience T1D only.

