#### Primary Outcomes

These include HbA_1c_ levels, percentage with HbA_1c_ <7.0%, and the number of hyperglycemic and hypoglycemic events.

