### Data Analysis

#### Statistical Analysis

The intention-to-treat principle will be used for the data analysis; that is, all participants will be included in their initially assigned groups for analysis, regardless of whether they withdraw from the study for any reason or are lost to follow-up. Data will be analyzed using IBM SPSS 26.0 for Windows, with differences considered statistically significant at *P*<.05. Demographic and disease status data, including age, gender, BMI, age at diagnosis, disease duration, and HbA_1c_, along with metrics on the app usage to evaluate treatment fidelity, such as the log-ins to the app, frequency of use for each interface, number of e-books read in the CEO Knowledge Base, and number of online consultations in CEO’s Secretary, will be presented through descriptive statistics. This will include frequency distributions, percentages, means, SDs, and maximum and minimum scores. Homogeneity in the essential attributes of the 2 groups will be compared and analyzed using inferential statistics, such as the chi-square test and ANOVA. Owing to the longitudinal nature of this study, repeated data measurements will be taken. Dependencies may exist among the data at different time points, and data loss may also occur. Using generalized estimating equation models, repeated measurements can be simultaneously included in the regression analysis. Through the variance correction process, consistent estimates of the regression parameters and their variance can be provided to correct for dependencies, and participants with missing values can still be included in the analysis [52]. Therefore, a generalized estimating equation will be used for data analysis to compare the differences between the experimental and control groups at both preintervention and postintervention time points, as well as the differences in the scores of the experimental group before and after intervention.

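### Before/after change in the experimental arm alone is listed as an efficacy analysis, but it cannot separate an app effect from change common to both arms

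*Protocol article*

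**What the plan says.** Three places in the protocol article fix the analysis.

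- **Introduction, Knowledge Gaps.** The purpose is stated as "This study aims to present a comprehensive protocol for evaluating the efficacy of the Healthcare CEO app". Two numbered analyses follow: (1) the between-group comparison, and (2) "a comparison of differences in preintervention and postintervention disease control outcomes", together with self-management confidence, self-care behaviors, emotional distress and quality of life, in the experimental group.
- **Abstract, Methods.** After the between-group comparison it adds that "changes within the experimental group will be analyzed before and after the intervention".
- **Methods, Statistical Analysis.** One GEE sentence covers the between-group differences "as well as the differences in the scores of the experimental group before and after intervention". The section has one significance rule, "with differences considered statistically significant at" P<.05, and gives the within-arm comparison no separate status.

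Two further places bear on what a within-arm change means. Entry requires "mean HbA_1c_ level ≥7.5% one year before inclusion" (Inclusion and Exclusion Criteria), and HbA1c is itself primary: "These include HbA_1c_ levels, percentage with HbA_1c_ <7.0%, and the number of hyperglycemic and hypoglycemic events" (Primary Outcomes).

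**The concern.** The question is whether the app works. A change from T0 in the experimental arm estimates the app effect plus everything else that moves the outcome over nine months. From the document, that includes:

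- the same questionnaires completed at four time points;
- contact with the trial at each data collection, and the message to every participant that using the app may help (Randomization and Blinding);
- the Health Tracking function, which the control app also contains (Control App Intervention);
- time trends, in a trial whose recruitment stopped and restarted (Results);
- possibly regression to the mean, because participants are selected on past values of a primary outcome.

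The control arm experiences all of these, so the difference in change between arms removes them. The single-arm comparison does not.

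With two efficacy analyses listed together and no ranking, a trial with no difference between arms but a significant change in the experimental arm could be written up as showing effectiveness without departing from the protocol.

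**Working it through.** **Step 1. What the trial is sized for.** Inputs from Sample Size: f = 0.25, correlation 0.5, alpha .05, power 0.80, 2 groups, 9 measurements. For a repeated-measures between-groups test, λ = f²·N·m/(1+(m−1)ρ), with 1 and N−2 degrees of freedom. At N = 72 and m = 9, λ = 0.0625×72×9/(1+8×0.5) = 8.1 and power is 0.801. That gives 36 per group, and 72/0.75 = 96. Within-factor or interaction settings give N = 16 with 9 measurements or 24 with 4, so of the settings tried only the between-group test with m = 9 reproduces the plan's figure.

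**Step 2. Regression to the mean, simple form.** Assume the registry figures cited in the Background (mean 8.7, SD 1.9) describe the one-year mean before selection.

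- z = (7.5−8.7)/1.9 = −0.632; proportion selected = 0.736.
- Excess of the selected mean = 1.9×φ(z)/0.736 = 1.9×0.327/0.736 = 0.843 points.
- Drift from T0 to T3 = (r0−r3)×0.843, where r0 and r3 are the correlations of the one-year mean with T0 and T3. Neither is in the document. With r0 = 0.9, r3 = 0.8 gives 0.084 and r3 = 0.7 gives 0.169.

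**Step 3. Regression to the mean, by simulation.** Quarterly HbA1c values from 12 months before T0 to 9 months after were simulated with mean 8.7 and SD 1.9, keeping those with a qualifying four-value mean of at least 7.5 and no app effect.

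| Correlation over time | T0 and the qualifying mean | Fall, T0 to T3 | Within-arm P<.05, n=36 |
|---|---|---|---|
| Constant, 0.5-0.7 | T0 outside | 0.00 | 5% |
| Constant, 0.5-0.7 | T0 included | 0.07-0.11 | about 6% |
| Decaying, 0.7-0.9 per quarter | either | 0.18-0.36 | 11-18% |

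**Step 4. Rejection by a within-arm test.** A two-sided paired t test stands in for the GEE pre/post contrast. SE = SD·√(2(1−ρ)/36), with noncentrality drift/SE. Assumed ranges are SD 1.5-1.9 and T0-T3 correlation 0.5-0.8, so SE runs from 1.5×√(0.4/36) = 0.158 to 1.9×√(1/36) = 0.317.

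| Change with no app effect | Within-arm rejection |
|---|---|
| 0.10 points | 6-9% |
| 0.17 points | 8-18% |
| 0.30 points (hypothetical, any shared cause) | 15-45% |

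**Step 5. The between-group test under the same shared change.** With 36 per arm, SD of change 1.9 and shared changes from 0 to 0.8 points, the simulated between-group rejection rate was 4.9-5.4%. At 0.3 points the within-arm test rejected in 16% of the same simulated trials.

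**Step 6. Scope of analysis (2).** It covers four disease control outcomes (HbA1c, percentage below 7.0%, hyperglycemic events, hypoglycemic events) plus confidence, self-care, distress and quality of life: eight outcomes. Knowledge is not among them. The Statistical Analysis section does not say that each follow-up is tested separately against baseline.

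**The case against.** The strongest reply is that the trial already has the right test. The between-group comparison comes first in every statement of the analysis, the abstract brings in the within-arm change only as an addition, and the sample size reproduces only as a between-group calculation. A within-arm test is also valid for its own hypothesis of no change over time, and misleads only if it is read as efficacy. This stands as far as it goes: the trial is not without a valid analysis. It does not answer the point, because Knowledge Gaps itself places the within-arm comparison under the evaluation of efficacy.

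A second reply is that ranking the analyses belongs in a statistical analysis plan, which is not shown. Detail may be left there, but the objection here is to a status that the article states.

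A third reply concerns size, and much of it stands. Selecting on a one-year mean weakens regression to the mean. The correlations are assumed. The registry figures are from the United States for ages 18-25, and the 0.3-point shared change has no source in the document. The direction is open too: the article describes deteriorating control at this age, which would push HbA1c up and could hide a benefit in a single-arm comparison. The selection argument also bears mainly on the disease control outcomes, not the questionnaires.

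Two stronger readings are tempting. A reader might multiply nine outcomes by three follow-ups and claim 27 within-arm tests; Step 6 shows that the article supports neither factor. A reader might also infer that the sponsor intends to rest its conclusion on the within-arm result, or that the plan discards its control arm. No section says so, and the control arm is used in analysis (1).

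**Conclusion.** The concern holds in this form: pre/post change in the experimental arm is a stated efficacy analysis under the P<.05 rule, and it cannot isolate an app effect. That conclusion needs no assumption about size, since any change common to both arms enters the estimate.

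How often it would mislead is uncertain. Regression to the mean alone ranges from nil (constant correlation, T0 outside the qualifying mean), through about 0.1-0.2 points with rejection of about 6-18% at n=36, to about 0.36 points under decaying correlation. The 15-45% figure is an illustration for a hypothetical 0.3-point shared change, not a forecast. These figures rest on the registry mean and SD, the assumed correlations, and a paired t test standing in for the GEE contrast.

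A reader might infer that the high-HbA1c entry rule is the main source of bias. The document does not support that, because this component may be zero. The between-group comparison, its near-5% error rate under shared change, and the sample size are unaffected.

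**What to change.** Change the wording in three places: Abstract (Methods), Knowledge Gaps, and Statistical Analysis.

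- State that effectiveness is judged only on the between-group difference in change from baseline, that is, the group-by-time contrast from the GEE already planned.
- Present within-arm changes for both arms side by side, as descriptive estimates with confidence intervals and no significance test.

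No new data, participants or sample-size change are needed. The cost is that the sponsor gives up within-arm P values as supporting evidence.

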#### Conceptual Framework of the Study

Based on the literature described above, the transition phase theory was used as the framework of this study [6,40]. According to the transition phase theory, antecedents that trigger transition can be classified into 4 categories: developmental, situational, health illness, and organizational transitions. The Healthcare CEO app will be used as an intervention measure for patients with T1D transitioning from adolescence to early adulthood, and the effectiveness of the intervention in improving disease control outcomes, confidence in disease self-management, self-care behaviors, emotional distress, and QoL will be investigated, as shown in Figure 1.

**Figure 1 figure1:**
[figure not shown]
Conceptual framework of the study. HbA_1c_: hemoglobin A_1c_; QoL: quality of life.

## Methods

### Design

A 9-month, 2-arm, parallel-group, double-blind, randomized controlled trial will be conducted. Participants will be randomly assigned to the experimental or control groups, and treatment fidelity monitoring strategies will be adopted to enhance the consistency and fidelity of intervention measures.

### Participants

#### Inclusion and Exclusion Criteria

Participants will be enrolled from the outpatient clinic and wards of the Department of Pediatric Endocrinology and Metabolism, at a medical center in Northern Taiwan. The inclusion criteria are as follows: (1) a confirmed diagnosis of T1D from an endocrinologist before the age of 16 years and a disease duration of >6 months; (2) aged 16-25 years; (3) mean HbA_1c_ level ≥7.5% one year before inclusion; (4) ability to communicate in Chinese or Mandarin; (5) owning a smartphone with internet access; (6) agreeing to voice recording while explaining the treatment process; and (7) signing the informed consent sheet prior to participation—for minors, a legal representative must provide consent and sign the informed consent sheet. Patients with T1D with concomitant metabolic diseases, chromosomal aberrations, major illnesses, and cognitive impairment will be excluded from the study because their health care needs during the transition phase may differ from those who experience T1D only.

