### Randomization and Blinding

Randomization of the participants will be performed by a statistician, using the central randomization method in SPSS (IBM Corp). During participant enrollment, participants will be randomly assigned to the experimental or control groups in accordance with the instructions provided on the phone by the statistician; the participants and data collectors will be blinded to allocation. Blinding strategies include the following. First, the statistician will not be allowed to disclose the randomization results to others. Second, once a physician referral is received, the participant will be promptly taken to a private room. The data collection assistant will complete their duties and leave the room, and then 2 research assistants will come in and take over to administer the intervention phase. Third, participants of both the experimental and control groups will download the app, but the app content will differ. Fourth, to avoid differential demand characteristics, research assistants will emphasize to all participants that app usage is potentially beneficial for disease management.

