##### Hyperglycemic Events

The number of events with blood glucose >200 mg/dL or “high” on the glucometer or diagnosed ketoacidosis will be calculated for each participant.

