##### Hypoglycemic Events

The number of events with blood glucose <60 mg/dL or “low” on glucometer or diagnosed hypoglycemia will be calculated for each participant.

For hyperglycemic and hypoglycemic events, during the data collection period, the blood glucose readings will be downloaded from the blood glucose meters of the participants, and the number of hyperglycemic and hypoglycemic events will be calculated. Considering that changes in blood glucose levels may be tracked only after adopting treatment measures, 2 researchers will perform a manual inspection of the data simultaneously. Only the first recorded reading, among all readings taken within the same measurement period, will be analyzed.

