### Data Collection

Three research assistants with a background in health care, who have a basic understanding of T1D, have undergone training, and are not involved in the provision of health care, will be responsible for the data collection. Attending physicians of patients with T1D will provide referrals of patients who meet the inclusion criteria. One research assistant in charge of data collection will then approach the patients to explain the purposes of the study and the research process. Patients who agree to participate will subsequently fill out the informed consent sheet and undergo the preintervention test (T0) in an undisturbed environment. The second research assistant will obtain the randomization results from the statistician by phone and assist participants in downloading the Healthcare CEO app onto their smartphones based on their group assignment. The third research assistant will check and remind the second research assistant of the intervention steps to ensure the accuracy and completeness of the intervention. Considering that HbA_1c_, the critical indicator of blood glucose control, is measured once every 3 months, the time points for the postintervention data collection for both groups are set at 3 months (T1), 6 months (T2), and 9 months (T3) after the intervention.

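### Ward inpatients take T0 at the recruitment encounter, so natural recovery can bias the experimental-group before/after comparison in the app's favour; the randomised comparison stays unbiased.

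*Protocol article*

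**What the plan says.** Recruitment has two settings (Inclusion and Exclusion Criteria): "Participants will be enrolled from the outpatient clinic and wards of the Department of Pediatric Endocrinology and Metabolism". One T0 procedure serves both. Under Randomization and Blinding, "once a physician referral is received, the participant will be promptly taken to a private room". Under Data Collection, "Patients who agree to participate will subsequently fill out the informed consent sheet and undergo the preintervention test (T0) in an undisturbed environment"; a second assistant then gets the allocation by phone and helps install the app. No interval for recovery or discharge is described.

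The Background says of this age group that "patients often become hospitalized owing to acute complications such as ketoacidosis and hypoglycemia", and adds that going from hospital to home disturbs daily routine.

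Two primary outcomes count the same kinds of event. The rule in the section on hyperglycemic events reads: "The number of events with blood glucose >200 mg/dL or “high” on the glucometer or diagnosed ketoacidosis will be calculated for each participant". The section on hypoglycemic events has a parallel rule, met by a reading under 60 mg/dL, a low display on the meter, or a diagnosis of hypoglycemia. The period over which events are counted at T0 is not given.

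Two comparisons are planned (Knowledge Gaps, aims 1 and 2; Statistical Analysis). One is experimental against control. The other is before against after within the experimental group alone. Generalized estimating equations (GEE) are to be used for both.

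**The concern.** T0 need not mean the same thing for the two kinds of recruit. A clinic patient answers the questionnaires in ordinary life. A ward patient admitted with ketoacidosis or hypoglycemia answers questions on distress, confidence, self-care and quality of life during that admission, and the admission diagnosis may itself be a T0 event. By 3, 6 and 9 months the episode is over.

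Such patients tend to improve from T0 whichever version of the app they have. The control arm absorbs this in the randomised comparison. The experimental-group before/after comparison has no control arm, so the recovery is read as benefit. This is bias, and a larger sample does not reduce it. The entry rule of a mean HbA1c of at least 7.5% over the preceding year selects on poor control in both settings and can add regression to the mean in the same direction.

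At stake is aim 2, together with some precision in aim 1.

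**Working it through.** **The plan's own figures.** The article gives no ward share and no size for any T0 shift, so it has no figure on this point to reproduce. Its dropout step is consistent: 36 / (1 − 0.25) = 48 per arm. Nothing in the sample size depends on setting.

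**Inputs from the article.** 36 per arm before dropout, 48 per arm enrolled, correlation 0.5 (Sample Size). HbA1c SD 1.9%, from a US registry of 18- to 25-year-olds cited in the Background, used here for want of a trial-specific value.

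**Assumptions.** Ward share w; a T0 shift in ward patients only, gone by follow-up; no true app effect.

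**Step 1: before/after within the experimental arm.** The expected false change is w × shift. It was simulated with 36 per arm, correlation 0.5, outcomes in SD units and 4,000 trials per row, comparing T0 with one follow-up visit by t tests at 5%.

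| Ward share | Shift (SD) | False improvement (SD) | Within-arm rejection | Between-arm rejection |
|---|---|---|---|---|
| 10% | 0.5 | 0.05 | 5.5% | 5.1% |
| 10% | 1.0 | 0.10 | 8.2% | 4.5% |
| 20% | 0.5 | 0.10 | 9.4% | 4.5% |
| 20% | 1.0 | 0.20 | 18.7% | 5.2% |
| 30% | 0.5 | 0.15 | 13.5% | 4.5% |
| 30% | 1.0 | 0.30 | 36.0% | 4.8% |
| 50% | 0.5 | 0.25 | 28.9% | 5.1% |
| 50% | 1.0 | 0.50 | 75.2% | 5.2% |

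Sample size does not help. At 20% and 1 SD the SD of change is 1.08. With 36 patients the standard error is 1.08 / √36 = 0.18, and the bias of 0.20 is 1.1 standard errors. With 48 it is 1.08 / √48 = 0.156, and the same bias is 1.3 standard errors.

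**Step 2: between arms, in expectation.** In the same simulation the mean between-arm difference in change is 0.00 and rejection stays at 4.5–5.2%. Randomisation does its work.

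**Step 3: between arms, precision.** Take HbA1c with 48 per arm, w from 10% to 30%, and an assumed T0 excess δ of 1 to 2 points in ward patients.

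- Variance of change without ward mixing: 2 × (1 − 0.5) × 1.9² = 3.61.
- Standard error of the arm difference: √(2 × 3.61 / 48) = 0.39.
- Added variance w(1 − w)δ²: 0.09 × 1 = 0.09 at the low end, 0.21 × 4 = 0.84 at the high end.
- Ratio of standard errors: √(3.70 / 3.61) = 1.012 and √(4.45 / 3.61) = 1.110.

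The standard error rises by about 1% to 11%.

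**Step 4: imbalance and added variance are one quantity.** The SD of the chance difference in ward share between arms is √(2w(1 − w) / 48), which is 0.061 at 10% and 0.094 at 30%. Times δ this is 0.06 to 0.19 HbA1c point. The added variance from Step 3 gives the same: √(2 × 0.09 / 48) = 0.061 and √(2 × 0.84 / 48) = 0.187. Chance imbalance is therefore already counted in the 1–11%.

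**The case against.** The strongest reply is that ward patients may be few and need not be acutely ill when they answer. The sentence about taking the patient promptly to a room is one item in a list of blinding measures. It governs who is present, not the day of the admission. The attending physician decides when to refer, and that could be near discharge. The statement that admissions are often acute is literature background, not a description of this site. All of this stands: ward share, reason for admission and timing are unknown, and if wards supply almost nobody the effect is negligible. But nothing described prevents T0 during the episode, and no setting is recorded in the measures listed.

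Silence on stratification is not a fault either, since an article condenses the full protocol and allocation details often sit elsewhere. Stratifying is offered here as an improvement.

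Three stronger readings are tempting, and the article does not support them.

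- A reader might infer that the treatment effect itself is biased. It is not: both arms draw on the same settings at random.
- A reader might infer that every outcome is distorted. The article treats HbA1c as a slow marker ("HbA_1c_, the critical indicator of blood glucose control, is measured once every 3 months"), so one episode should move it little, and no reason appears why an admission would change knowledge. The 1–2 point shift in the working is at the generous end.
- A reader might infer that event counts start at one or more for patients admitted with ketoacidosis or hypoglycemia. That holds only if the T0 look-back includes the admission, and in poorly controlled patients one episode may add little to a count already above zero.

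**Conclusion.** The point holds for the uncontrolled before/after comparison in the experimental group. For ward patients admitted with an acute complication, T0 event counts (subject to the look-back), distress, confidence, self-care and quality of life can reflect the episode, and recovery then favours the app by about ward share times shift. Over assumed shares of 10–50% and shifts of 0.5–1.0 SD, that is 0.05 to 0.50 SD of false improvement.

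The randomised comparison remains valid. It loses about 1–11% in standard error for an assumed 10–30% ward share and 1–2 point HbA1c shift, and probably less, because HbA1c is unlikely to shift that far. All sizes rest on shares and shifts that the article does not give. This is a modest issue that is cheap to improve, and no threat to the trial's main comparison.

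**What to change.** 1. Record recruitment setting (clinic or ward) for every participant, including the 38 enrolled before the halt and anyone enrolled since, and report the numbers by arm.
2. Stratify the remaining central phone allocations by setting.
3. Include setting and setting-by-time in the GEE, so that a different course in ward patients is modelled and not left in the residual.
4. Base conclusions on effectiveness on the group-by-time contrast. Keep the within-arm change, but label it descriptive. Modelling setting does not turn it into an estimate of the app's effect.

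The cost is one stratification factor in an allocation already made centrally, a few model parameters, and looking up the setting of those already enrolled.

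Moving T0 and allocation for ward patients until after discharge is optional and a trade-off. It would bring T0 closer in meaning across settings for the questionnaires, but it delays the start and may lose patients. It also drops the hospital-to-home period, which the article's own framework treats as part of the transition, and it may not clear the episode from HbA1c or from the event look-back.
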